### 2.11. Data Management and Statistical Analysis Plan

The principal investigator will have exclusive responsibility for the data and will retain an offline copy on a secure hard drive. The anonymized data will be stored in an open-access repository (Zenodo.org) and may be shared with other researchers upon reasonable request.

The initial analytical approach will comprise descriptive statistics and data visualization to perform an exploratory assessment of the dataset, including an evaluation of bivariate associations between the predictor variables (nut consumption doses) and the outcome variables (mental health parameters). This stage will assess potential baseline differences among the three groups (CG, IG-30, and IG-60).

Subsequently, assumptions of normality and homoscedasticity for the outcome variables will be examined to ascertain the suitability of employing a repeated-measures mixed-effects model to characterize the intervention relationship between nut consumption and mental health indicators. Interpretation will focus on the magnitude and statistical significance of the fixed effects coefficients, thereby determining whether nut consumption is associated with changes in mental health outcomes and whether these associations vary across study intervention groups.

The role of BDNF will also be analyzed, examining associations between BDNF changes and mental health measures through correlation analysis at each timepoint, mediation analyses using structural equation modeling to test whether BDNF mediates the relationship between nut consumption and mental health, including cognitive improvements, and dose–response analyses across study arms. Secondary exploratory analyses will include responder analyses (BDNF increase), time-course analyses using linear mixed models, and interaction analyses examining moderators such as baseline BDNF levels and mental health status. All BDNF-cognition analyses will be designated as secondary/exploratory with appropriate adjustments for multiple comparisons and covariates, including age, sex, baseline cognitive performance, physical activity, and dietary quality.

The intention-to-treat (ITT) analysis will serve as the primary analysis to preserve randomization benefits and provide a conservative estimate of treatment effects, whereas the per-protocol (PP) analysis will serve as a sensitivity analysis to assess efficacy under optimal adherence conditions. The ITT analysis will include all randomized participants in their assigned groups regardless of adherence, with missing data handled using multiple imputation or mixed-effects models that accommodate incomplete observations. The PP analysis will include only participants who completed the intervention according to protocol specifications, with adherence thresholds defined a priori (e.g., self-reported consumption of at least 80% of nut doses assigned, and 5–15% increased blood concentrations of α-tocopherol) [61].

The interpretation of clinical significance will be based on established minimal clinically important differences (MCID) for each outcome measure. For example, for the BDI-II, we will apply a 17.5% reduction as determined by Button et al. (2015) [100], who found that this represents the threshold at which patients report feeling “better” based on anchor-based methods. We will also evaluate whether participants transition between established severity categories (minimal: 0–13; mild: 14–19; moderate: 20–28; severe: 29–63) [63]. For the GAD-7, we will use the 4-point MCID threshold established by Toussaint et al. (2020) [101] to assess whether participants cross the clinical cut-off of ≥10 points, indicating clinically significant anxiety [66]. Given the lack of consensus on the MCID for the PSS-10, we will interpret effect sizes of Cohen’s d ≥ 0.5 as clinically relevant [57] and contextualize changes using reference values for the target population [102]. We recognize that in preventive nutritional interventions targeting non-clinical populations, small but consistent effects may have beneficial public health impacts [103], particularly given that dietary modifications represent accessible and low-risk interventions.

The results will be considered statistically significant at the α = 0.05 level. In the presence of statistically significant effects, post hoc analyses will be conducted using a pairwise comparison test to delineate specific contrasts between each intervention group and the control arm. Furthermore, statistical and clinical significance will be distinguished in our discussion, considering both the magnitude of effects and their potential implications for guidelines recommending nut consumption as a strategy to prevent or improve mental health outcomes. Therefore, when the estimators of associations do not reach statistical significance due to the small difference between the intervention and control groups, the results will be presented for their descriptive value and to inform future RCTs exploring the relationship between nuts and mental health. Although *p*-values are relevant, changes that are not statistically significant can still be clinically meaningful [104].

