### 2.4. Sample Size Calculation

The sample size was calculated using the Grayling and Wason method for multi-arm trials [56], which is appropriate for a design with two experimental groups and one control group. A medium effect size (Cohen’s d = 0.5) and homogeneity of variance (σ = 1) were assumed across groups as recommended [57] when no clear estimate on this association is provided in the available studies with similar design [48,49]. With a two-sided α of 0.05 and 80% power (β = 0.20), the required sample size was obtained via the “des_ss_norm()” function in R statistical software, version 4.5.2 (R Core Team, 2024, Vienna, Austria). All three arms were allocated at a 1:1:1 ratio. To account for multiple comparisons, the Benjamini–Hochberg correction was applied to control the false discovery rate. The power calculation was based on a disjunctive criterion, which estimates the probability of detecting at least one significant difference between any intervention group and the control group. The initial calculation yielded a requirement of 42 participants per group. After accounting for an anticipated 20% dropout rate, the final sample size was adjusted to 53 participants per group. This resulted in a total target enrollment of 159 participants across all three study arms. The participants will initially be drawn from the 463 students enrolled in the Nuts4Brain-Z observational study (data collection September–December 2023) [58,59,60]. If necessary, recruitment will be extended to additional UCLM undergraduate students to reach the target sample size.

The sample size calculation was based exclusively on the primary outcome as we did not find previous studies examining the association between nut consumption and our secondary outcomes that would provide the necessary effect size estimates for power and sample size calculations. Consequently, the study should be considered exploratory with regard to these secondary outcomes, and any findings related to them should be interpreted with appropriate caution. While our sample size provides adequate power for detecting changes in the primary outcome, we acknowledge that it may be underpowered for detecting meaningful differences in secondary outcomes, particularly if the true effects are small to moderate in magnitude.

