### 2.8. Trial Monitoring

Every two weeks, all participants will receive a telephone message via WhatsApp from a member of the research team to reinforce adherence and monitor any adverse effects potentially associated with the intervention. If a participant experiences a suspected allergic reaction, intolerance, or digestive discomfort, the intervention will be immediately and permanently discontinued, and medical evaluation will be recommended.

Intervention compliance will be assessed according to the participants’ report of the consumption of at least 80% of the nut doses provided [61]. In addition, to provide an objective measure of adherence to the nut consumption protocol, blood concentrations of vitamin E (α-tocopherol) will be assessed in the four evaluations. Although the expected magnitude of increase in vitamin E associated with nut consumption varies by nut type, dose, and baseline levels, the available evidence has shown a 5 to 15% increase in plasma α-tocopherol with regular consumption of 30–80 g nuts/day over several weeks to month [62].

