#### 2.12.2. Contingency Plan

Recruitment and retention: If enrollment targets are not met, recruitment efforts will expand across the university. These efforts will use multiple communication channels, classroom presentations, and student organizations. If necessary, eligibility criteria may be slightly adjusted with ethical approval. If the number of students who drop out exceeds expectations, retention strategies will be intensified. These strategies include increased contact, flexible scheduling, reminders, small incentives, and feedback on selected results. Participants who are unable to continue in person will be encouraged to complete all self-reported assessments remotely to support intention-to-treat analyses.Intervention delivery: A backup nut supply and alternative suppliers will be maintained. Any adverse reactions will lead to immediate discontinuation and medical referral. Participants for whom poor adherence is detected during the intervention will receive individualized support and encouragement to remain in the study, regardless of their level of adherence.Data collection and analysis: Backup equipment and rescheduling windows will address equipment failure, technician strikes, and other unpredictable circumstances. Missing data, except for covariates, will be handled using multiple imputation and mixed-effects models. Sensitivity analyses will be performed to assess potential bias.External and ethical considerations: In the event of public health emergencies, such as the COVID-19 pandemic that emerged in 2020, assessments will shift to remote formats where feasible. Seasonal and academic calendar effects will be addressed analytically. Any protocol amendments will receive prior ethical approval, and robust procedures are in place to manage data security incidents.Monitoring and quality assurance: Study progress, adherence, retention, and data quality will be monitored monthly by the study coordinator and reviewed quarterly by the principal investigator. Serious adverse events or unexpected issues will prompt immediate review and, if needed, consultation with the ethics committee. Vitamin E (α-tocopherol) levels will be measured in all participants at baseline, 3 months, and 6 months, along with dietary intake assessments. Unauthorized nut consumption in the control group will be detected through either increases in vitamin E levels > 5% from baseline or self-reported nut intake in dietary recalls.Academic stressors and seasonal variations: The following strategies will be adopted to address confounding by academic-related stressors (e.g., examination periods, high academic demands) and seasonal factors: (1) randomization, to balance exposure to stressful periods across groups; (2) tracking assessment dates, to categorize examination periods and seasons; (3) repeated-measures mixed-effects models, adjusting for these factors as covariates; and (4) sensitivity analyses, to test the robustness of findings. Furthermore, stress is directly monitored as a primary outcome using the PSS-10 scale and may reflect partially academic-related stress symptoms.

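### The ITT analysis is called conservative, but with missing outcomes handled by mixed models or default multiple imputation this is not guaranteed: dropout from the nut arms can leave the effect overstated

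*Protocol article*

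**What the plan says.** Section 2.11 (Data Management and Statistical Analysis Plan) makes ITT the primary analysis. It includes everyone randomised, in the assigned arm and whatever their adherence, in order to "preserve randomization benefits and provide a conservative estimate of treatment effects". The same paragraph has "missing data handled using multiple imputation or mixed-effects models that accommodate incomplete observations". The per-protocol analysis, restricted to adherent completers, is the sensitivity analysis.

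Section 2.12.2 (Contingency Plan) restates the approach: "Missing data, except for covariates, will be handled using multiple imputation and mixed-effects models". It then promises sensitivity analyses for potential bias without giving their content. It also says that poor adherers will be encouraged to stay in the study, and that participants who cannot attend will be asked to complete the self-reports remotely.

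Section 2.8 (Trial Monitoring) states that after a suspected allergic reaction, intolerance or digestive discomfort "the intervention will be immediately and permanently discontinued". Some nut-arm participants will therefore be off nuts before the 6-month visit. Section 2.4 anticipates 20% dropout.

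**The concern.** Including everyone as randomised dilutes an effect only where the outcomes of people who stopped the intervention are actually measured. Where those outcomes are missing, the analysis has to predict them. A likelihood mixed model, or multiple imputation in its default form, does so under missing at random: a nut-arm dropout is given the outcome expected from their own earlier scores and the course of retained members of the same arm. If that person has stopped nuts and the benefit has gone, the prediction is too favourable. Under this mechanism the error is zero or upward, the opposite of what the label promises.

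The size of the effect matters here. Section 2.11 reads d of at least 0.5 on the PSS-10 as clinically relevant and ties the results to guidelines on nut consumption. A reader who has been told that the estimate is conservative will not look for an upward error. The point concerns the 3- and 6-month outcomes, because all participants are released from the dietary instructions after month 6.

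**Working it through.** **Inputs from the protocol article**
- On-nut effect: section 2.4 says "A medium effect size (Cohen’s d = 0.5) and homogeneity of variance (σ = 1) were assumed across groups", so D = 0.5 SD.
- Dropout: 20% (section 2.4), so p = 0.20.

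**The plan's own figures.** 42/(1 − 0.20) = 52.5, rounded up to 53 per arm, and 3 × 53 = 159, as stated. About 0.20 × 53 = 10.6 participants per arm are therefore expected to be unobserved. (How the 42 was obtained is a separate matter and does not enter this check.)

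**Assumptions not in the protocol**
- r = share of the effect that dropouts keep, varied from 0 to 1.
- s = share of retained nut-arm participants who are non-adherent but measured, set to 0 or 0.20; they keep the same share r.
- Control dropouts do not differ from retained controls.

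**Formulas**
- Target of a missing-at-random analysis (the mean of the retained arm): M = (1 − s)D + s·r·D.
- Effect in all randomised participants under actual adherence: T = (1 − p)M + p·r·D.
- Overstatement: M/T − 1. With s = 0 this is 1/[1 − p(1 − r)] − 1.

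**Results with s = 0, so M = 0.50**

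| Dropout p | Share of effect kept r | T | Overstatement |
|---|---|---|---|
| 10% | 0 | 0.90 × 0.5 = 0.45 | 11% |
| 10% | 0.5 | 0.45 + 0.10 × 0.25 = 0.475 | 5% |
| 20% | 0 | 0.80 × 0.5 = 0.40 | 25% |
| 20% | 0.5 | 0.40 + 0.20 × 0.25 = 0.45 | 11% |
| 20% | 1 | 0.50 | 0% |
| 30% | 0 | 0.70 × 0.5 = 0.35 | 43% |
| 30% | 0.5 | 0.35 + 0.30 × 0.25 = 0.425 | 18% |

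If only half of the 20% are off nuts and those lose everything, T is again 0.45 (11%).

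**With measured non-adherers** (s = 0.20, r = 0, p = 0.20): M = 0.80 × 0.5 = 0.40 and T = 0.80 × 0.40 = 0.32. The observed non-adherence is counted correctly and pulls the estimate below the on-nut 0.50. Only the dropouts' share of the error remains.

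**With no nut effect:** D = 0 gives M = T = 0, so the gap vanishes.

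**Simulation check** (400,000 per arm; baseline, 3 and 6 months; assumed visit correlation 0.6; within-arm missing-at-random prediction), for 20% dropout:
- whole effect lost: 0.501 reported against 0.402 true;
- half kept: 0.496 against 0.445;
- all kept: 0.502 against 0.501;
- whole effect lost and 20% measured non-adherers: 0.405 against 0.322.

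These agree with the formulas. The no-effect case rests on the formula alone.

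**The case against.** The strongest reply is that the word is meant relative to the per-protocol analysis, which the same sentence goes on to describe. Where non-adherers stay and are measured this is right: in the case above ITT gives 0.40 against 0.50 on nuts. It does not hold in general. If those who stop nuts mostly leave, s tends to 0, M returns to 0.50, and ITT and per-protocol converge.

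The second reply is that the plan already works against the problem. Stopping nuts under section 2.8 is not leaving the trial, poor adherers are kept, and BDI-II, GAD-7 and PSS-10 can be completed remotely. This stands, and it reduces the problem for those three scales. It does not reach the NIH Toolbox, which trained staff administer (section 2.10.1), or BDNF, which needs a venous sample (section 2.10.3). The Abstract lists both among the primary outcomes.

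Third, neither section fixes the imputation model, so multiple imputation could be control-based, and section 2.12.2 does promise sensitivity analyses. Their detail may properly sit in a fuller document, and its absence from the article is not held against the plan. But the property is claimed here, for methods that do not deliver it in their default form. The one analysis that section 2.11 names as a sensitivity analysis, per-protocol, drops non-adherers and so cannot test optimism about dropouts. Agreement between a mixed model and default multiple imputation would not test it either, since both rest on missing at random.

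Two stronger readings are tempting and are not supported:
- That the effect *will* be overstated. This needs a real benefit, dropouts who have stopped nuts, and a benefit that fades. The documents establish none of these, and the cause of attrition that section 2.12.1 names is assessment burden, which falls on all arms. Nor are dropouts credited with full adherence: they receive what is predicted from the retained arm, measured non-adherers included.
- That the false-positive rate is inflated. Loss of an effect cannot bias a comparison in which there is no effect. Such inflation would need a separate assumption, that nut-arm dropouts do worse than predicted for other reasons.

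**Conclusion.** The concern holds in a limited form. Calling the ITT estimate conservative is not justified by the stated handling of missing outcomes. At the planned 20% dropout and an assumed on-nut effect of 0.5 SD, the effect under actual adherence can be overstated by 0 to 0.10 SD, or 0% to 25%. The upper end is a worst case: every dropout off nuts with nothing of the effect left, and all retained participants adherent. The lower end applies if nuts do nothing, or if dropouts keep the effect or go on eating nuts. The range assumes that missing data are handled under missing at random, which is the default for both named methods but is not stated. The exposure is greatest for the outcomes that can only be measured in the clinic.

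**What to change.** 1. In section 2.11, delete the word conservative, or limit it to the comparison with per-protocol when non-adherers are retained and measured.
2. Name the mixed model as the single primary analysis, replacing the present choice between two methods in 2.11 and their combination in 2.12.2. State that it uses all outcomes observed after a participant has stopped nuts.
3. Specify one of the sensitivity analyses promised in section 2.12.2 as a control-based multiple imputation: missing nut-arm outcomes are drawn from the control-arm distribution given the participant's own earlier scores. A delta-adjusted imputation would also serve. Report it beside the primary result.

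The cost is a change of wording and one extra standard analysis, with a possibly less favourable estimate beside the primary one. The article describes itself as written before recruitment, so the change can be made before any data exist. No change to design, sample size or visits is needed.

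### The per-protocol rule turns an expected 5–15% rise in α-tocopherol into an individual band with a ceiling, and a 5% rise alone marks a control as a nut consumer, with no allowance for measurement variation

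*Protocol article*

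**What the plan says.** Section 2.11 makes intention-to-treat primary and says that "the per-protocol (PP) analysis will serve as a sensitivity analysis to assess efficacy under optimal adherence conditions". Membership of the per-protocol set is set "with adherence thresholds defined a priori (e.g".), and the example is "self-reported consumption of at least 80% of nut doses assigned, and 5–15% increased blood concentrations of α-tocopherol". The two conditions are joined by *and*, and the second, "5–15% increased blood concentrations of α-tocopherol", has a lower and an upper limit.

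The range comes from section 2.8, which cites evidence of a "5 to 15% increase in plasma α-tocopherol with regular consumption of 30–80 g nuts/day over several weeks to month". The same sentence warns that "the expected magnitude of increase in vitamin E associated with nut consumption varies by nut type, dose, and baseline levels".

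Section 2.12.2 uses the lower end of the range for the other arm: "Unauthorized nut consumption in the control group will be detected through either increases in vitamin E levels > 5% from baseline", or through self-reported intake. Either route is enough by itself.

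**The concern.** A range that describes what nut consumption is expected to do has become a test that each participant must pass. That causes three problems.

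- **The ceiling has no adherence rationale.** Rising more than 15% is not evidence of eating too few nuts, yet read literally it removes the participant from the set meant to show efficacy under optimal adherence.
- **The floor and the control flag are the same 5%.** This cut is the least that a full complier is expected to show, and it is also the point at which an abstainer is called a consumer. Both uses compare two blood samples, and neither allows for biological fluctuation or assay error.
- **The rule does not carry over to controls.** They have no assigned doses and are not expected to rise, so it does not say who counts as a per-protocol control.

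At stake are the meaning of the per-protocol sensitivity analysis, which would select partly on noise in a post-randomisation biomarker, and the reported amount of contamination.

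**Working it through.** The plan states no error rate for either rule, so there is no figure of its own to reproduce.

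**Step 1, without any CV.** A participant with 100% intake and a 16% rise meets the intake condition and fails the band, because 16 > 15. If measurement error is symmetric about the true change on the log scale, a complier whose true rise is exactly 5% or exactly 15% falls beyond that edge half the time. Such a person is therefore kept at most 50% of the time, however good the assay.

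**Step 2, inputs for the size.**
- Band 5–15%: section 2.11. Control flag above 5%: section 2.12.2.
- Total CV of one measurement (within-person plus assay): *assumed*, 2, 3, 5 and 10%. The only assay CV in the article, below 10%, is for BDNF (section 2.10.3).
- True rise of a complier: 10% as a central case (assumed). True change of an abstaining control: 0.
- One follow-up visit against baseline.

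**Step 3, formulas.** The ratio of follow-up to baseline is log-normal with s = √2 × √ln(1 + CV²). Φ is the standard normal distribution function.
- Control flagged: 1 − Φ(ln 1.05 / s)
- Complier kept, true rise t: Φ([ln 1.15 − ln(1+t)] / s) − Φ([ln 1.05 − ln(1+t)] / s)

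Worked case, CV 5%: s = 1.4142 × 0.04997 = 0.0707.
- Flag: ln 1.05 / s = 0.0488 / 0.0707 = 0.690, and 1 − Φ(0.690) = 0.245.
- Kept at t = 10%: Φ(0.629) − Φ(−0.658) = 0.735 − 0.255 = 0.480.

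**Step 4, results at one visit.**

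| Assumed CV | s | Complier kept (true +10%) | Below 5% | Above 15% | Complier kept (true +5% or +15%) | Abstaining control flagged |
|---|---|---|---|---|---|---|
| 2% | 0.0283 | 89.2% | 5.0% | 5.8% | 49.9% | 4.2% |
| 3% | 0.0424 | 71.6% | 13.6% | 14.7% | 48.4% | 12.5% |
| 5% | 0.0707 | 48.0% | 25.5% | 26.5% | 40.1% | 24.5% |
| 10% | 0.1411 | 25.3% | 37.1% | 37.6% | 24.0% | 36.5% |

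With the 42 controls of section 2.4, the flag column corresponds to about 2, 5, 10 and 15 false flags (42 × 0.042, 0.125, 0.245, 0.365).

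**Step 5, two visits.** If a control were flagged on a rise at *either* month 3 or month 6 (correlation 0.5 through the shared baseline), the rates would be about 7.5, 21, 37 and 52%. Section 2.12.2 does not state that rule, so these are a scenario only.

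**Step 6, what CV would justify the 5% cut?** A 5% false-positive rate at one visit needs a cut of exp(1.645 s) − 1, which is 4.8, 7.2, 12.3 and 26% for the four CVs. The 5% cut achieves this only if the CV is about 2.1% or less.

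**Step 7, dropping the ceiling only.** For a true 10% rise, adding the *above 15%* column to the *kept* column gives about 95, 86, 74.5 and 63% kept. The ceiling accounts for about half the loss and the uncalibrated floor for the rest.

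**The case against.** The best defence has five parts.

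- **The thresholds are only an example.** They follow *e.g.*, and the final definition may stand in a document not shown. This softens the point: one cannot say that the trial definitely requires the band. But the thresholds are described as set a priori and no others are offered.
- **At least 5% may have been meant, with 5–15% expected.** That is plausible given section 2.8, and it would remove the loss above 15%. The text does not say so, and the loss below 5% and the control flag would remain.
- **No α-tocopherol CV is given.** This stands. A reader might infer that 5% is simply the size of ordinary variation and that most compliers will be lost. The documents do not support that: at a CV of 2% only about 11% of compliers with a true 10% rise are lost (100 − 89.2) and about 4% of abstaining controls are flagged.
- **Extra loss in the 60 g arm is not shown.** It is tempting to infer that the ceiling removes more people there. Section 2.8 gives one range for 30–80 g/day and no gradient. It says the rise varies with dose, so differential loss is possible, but its size cannot be derived. Nor does the article say that the range is a mean across studies, or that people with the largest biomarker rise are those with the best outcomes.
- **A flagged control is not said to be excluded.** This is correct. Section 2.12.2 places the flag under monitoring and quality assurance, so it bears on the contamination count and not on a stated effect estimate.

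The biomarker is also there for a reason. Participants are unblinded and self-report can be biased, so discarding it would be a real loss.

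**Conclusion.** The point holds as a wording and justification fault in a stated rule. Read literally, section 2.11 excludes full compliers who rise more than 15% and keeps those whose true rise is at either edge at most half the time. Section 2.12.2 labels controls as nut consumers on a rise above 5% alone.

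The size is conditional on the assumed CV. At one visit, for CVs from 2 to 10%, between 89% and 25% of compliers with a true 10% rise are kept, and between 4% and 36.5% of abstaining controls are flagged. These figures assume log-normal error, independent samples and, for compliers, a common true rise of 10%. Spread in true rises adds its own loss: with mean 10%, SD 5 points (assumed) and no measurement error, about 32% fall outside the band, from 2 × [1 − Φ(1)].

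A reader might infer that the trial's main conclusion is at risk. It is not: intention-to-treat is primary, and only the per-protocol sensitivity analysis and the contamination count are affected.

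**What to change.** 1. In section 2.11, delete the 15% ceiling and stop using the 5–15% range as an individual inclusion rule. Define per-protocol as at least 80% of portions consumed in the nut arms and no reported direct nut intake in controls, with the trace amounts that section 2.7 already accepts.
2. Report the change in α-tocopherol by arm, with confidence intervals, at 3 and 6 months as the objective check on adherence and contamination.
3. If an individual biomarker cut is kept, make it one-sided and derive it from measured within-person plus assay variation, for example from changes in the control arm. Apply the same principle to the control flag in section 2.12.2 in place of 5%.
4. Fix these definitions before unblinding, so that the per-protocol set is not chosen after the results are seen.

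The cost is wording only, since self-reported intake and α-tocopherol are already collected. The downside is that individual adherence then rests more on self-report by unblinded participants. A per-protocol set supported by a calibrated biomarker cut can be shown as an additional sensitivity analysis to offset this.
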